### Participant adherence and co-interventions

The treating physiotherapist will record the number of treatment sessions attended for each participant, as well as any cancelled or missed appointments. Participant rating of adherence to physiotherapist advice will be recorded formally at each timepoint. Additionally, therapist and participant rating of participant adherence to advice will be recorded at each session. Any co-interventions will be recorded at each follow-up point.

### Data integrity

Outcome data will be stored within QuestionPro and downloaded to an electronic spreadsheet by a research assistant who will be blinded to the group allocation of participants. QuestionPro logs a date-stamp for each questionnaire completed, enabling researchers to monitor completion rates and follow-up missing questionnaires. Data will be reviewed for missing and outlier data to screen for potential data entry errors.

### Blinding

It is not feasible to blind participants or treating physiotherapists due to the nature of the interventions. However, treating practitioners and researchers will inform participants that both treatment approaches have a realistic chance of providing success and that neither has been shown to be superior in previous trials. Physiotherapists will be advised to treat both groups of participants with the same level of expectation and enthusiasm. Strength outcomes will be measured by a blinded assessor. Data analysis will be performed using data without identifying group labels, to ensure blinded analysis.

### Data analysis

#### Sample size

There are no trustworthy data for the VISA-H or other relevant outcome measures for PHT to inform sample size calculations. A sample size of 100 was therefore pragmatically chosen for this pilot study to provide sufficient data to facilitate an accurate sample size calculation and determine the feasibility of future trials on this population. A sample size of 100 would provide 80% power to detect a between-group standardised mean difference of at least 0.6 on continuous outcome measures such as the VISA-H, allowing for a 10% loss to follow up [99]. As smaller effect sizes would still be considered clinically important, this will not be a fully powered trial and is therefore considered a pilot trial.

#### Feasibility

We will aim for a recruitment rate of 12 participants per month. We will aim for greater than 85% participant retention and outcome measures completed, in line with the PEDro scale [100]. A slower recruitment rate would increase the cost and time-commitment of a larger trial.

#### Treatment effects

Following trial completion, data from all follow-up points (4, 12, 26- and 52-weeks following randomisation) will be analysed, focussing on between-group treatment effects (with 95% confidence intervals). SPSS will be used to conduct analyses. Alpha will be set at 0.05 using a two-tailed hypothesis.

Intention to treat principles will be used for all analyses; with participants analysed based on their original allocation regardless of their adherence with treatment or number of sessions attended [101]. Missing data will be managed by maximum likelihood estimation within linear mixed models [102].

Continuous data will be analysed using linear mixed models, adjusting for baseline values and the stratification variable of age (with the group x time interaction estimating the between-group treatment effect). Ordinal data will be analysed using the Mann Whitney U test at each timepoint. It is acknowledged that this will increase the Type 1 error rate however this only applies to some secondary outcomes and is offset in part by the lower power associated with non-parametric tests.

A responder analysis will also be undertaken to determine the proportion of participants who achieved clinically important changes on outcome measures. For these purposes, the minimum clinically important difference (MCID) for individuals will be defined as 12 points on the VISA-H questionnaire [72], and at least ‘much improved’ on the global rating of change scale [103, 104]. The MCID value for the VISA-H was used as it is similar to MCID values on other VISA scales [105–108]. For responder analyses, the risk ratio, risk difference and number needed to treat will be calculated along with 95% confidence intervals [109]. Statistical significance for the responder analyses will be evaluated using Chi square analysis.

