### Randomisation and allocation

Following provision of written consent, participants will be randomised into one of two intervention groups: PHYSIOTHERAPY or SHOCKWAVE. A researcher located remotely at La Trobe University who will have no contact with trial participants will prepare a randomisation schedule ahead of time. The randomisation sequence will be generated electronically by an online randomisation program that incorporates random block sizes. Randomisation will be stratified for age (< 50 years of age vs >  = 50 years of age), as systemic factors associated with menopause may influence response to some components of treatment [52–55]. Concealed allocation of participants in accordance with the randomisation schedule will be undertaken by the same researcher at La Trobe University who will be the only person with access to the allocation spreadsheet during the trial. To enrol a participant, the primary researcher (AR) will email the consenting participant’s name and date of birth to the La Trobe University researcher, who will enter the patient into the trial and notify the primary researcher of the treatment group allocation. These details will be entered into the allocation spreadsheet and the next intervention allocation and participant identification number will be emailed to the primary researcher who will contact the treating physiotherapist who will arrange the initial appointment.

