**Secondary outcome measures**	
1. Sitting tolerance (5-point scale)	0, 4, 12, 26, 52
2. Modified Physical Activity Level Scale (6-point scale)	0, 4, 12, 26, 52
3. Eccentric hamstring strength (nM)	0, 12
4. Modified Tampa scale for kinesiophobia (TSK-11) (11-item questionnaire)	0, 4, 12, 26, 52
5. Örebro Musculoskeletal Pain Screening Questionnaire Short Form (ÖMPSQ-SF)	0, 4, 12, 26, 52
6. Pain Catastrophizing Scale (PCS)	0, 4, 12, 26, 52
7. Numerical Pain Rating Scale (average and most severe pain over previous week)	0, 4, 12, 26, 52
8. Participant and physiotherapist rating of adherence (11-point Likert scale)	4, 12, 26, 52
9. Satisfaction with treatment (5-point Likert scale)	4, 12, 26, 52
10. Satisfaction with the results of treatment (5-point Likert scale)	4, 12, 26, 52
11. EuroQoL-5D	0, 4, 12, 26, 52

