## Discussion

In this pilot RCT we aim to compare individualised physiotherapy to ESWT in people with PHT. We hypothesise that participants receiving the individualised physiotherapy program (consisting of a multi-stage, graded strength/rehabilitation exercises) will achieve superior long-term (12 weeks and greater) clinical outcomes to participants who receive ESWT. There may be superior outcomes in the short term (< 12 weeks) in the SHOCKWAVE group due to the analgesic response of ESWT.

We will be testing this hypothesis in a population with longstanding, non-compensable PHT. We are including adult participants with varying levels of sporting participation. This decision was made both to aid recruitment, and to increase generalisability of trial findings. We will avoid including participants with acute or sub-acute PHT as these “reactive” tendinopathies are more likely to settle with short-term reduced load [5] and ESWT may be less likely to be beneficial [110].

To maximise treatment fidelity we will be using strategies similar to those in previous physiotherapy trials [46]. These include a detailed treatment manual, small group training of physiotherapists in the trial, algorithmic clinical note templates, and standardised participant information/advice sheets. Use of multiple stages in rehabilitation and algorithmic treatment approaches allow treatment to be as specific and relevant for participants as possible. As an example, a participant with a goal of returning to tennis may be prescribed lunges as part of their rehabilitation to simulate the demands of volley and backhand strokes. The rehabilitation may progress by modifying joint angles (specifically hip flexion) and eventually by adding speed. In contrast a participant with a goal of returning to walking may not require all of these components of rehabilitation.

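### The group-by-time interaction named as the treatment effect measures how the effect changes between follow-up visits, so the sentence should name the adjusted group difference at each visit instead

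*Protocol article*

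**What the plan says.** The Treatment effects section states that "data from all follow-up points (4, 12, 26- and 52-weeks following randomisation) will be analysed, focussing on between-group treatment effects (with 95% confidence intervals". It then specifies linear mixed models for continuous data, "adjusting for baseline values and the stratification variable of age (with the group x time interaction estimating the between-group treatment effect". Testing is two-sided: "Alpha will be set at 0.05 using a two-tailed hypothesis". The section does not give a reference visit, a coding of time, or a contrast at each visit.

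Three other places bear on this:

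- **Sample size:** "A sample size of 100 would provide 80% power to detect a between-group standardised mean difference of at least 0.6 on continuous outcome measures", "allowing for a 10% loss to follow up". The VISA-H is given as the example.
- **Table 2:** VISA-H is measured at weeks 0, 4, 12, 26 and 52. The row "Eccentric hamstring strength (nM" lists weeks 0 and 12 only.
- **Discussion:** physiotherapy is hypothesised to be superior from week 12 on. For the period before week 12 the text says "There may be superior outcomes in the short term" in the shockwave group. No sizes are given for either.

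**The concern.** The listed responses are the follow-up visits, and baseline enters as a covariate. In such a model the interaction answers whether the between-group difference changes across weeks 4 to 52. It does not answer how large that difference is at any visit. An arm that is better by the same amount from week 4 to week 52 has a real effect and no interaction.

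The sentence governs VISA-H and every continuous secondary outcome. The Discussion says the pilot will supply effect-size estimates for planning a later trial, so an interaction coefficient reported as the treatment effect could be carried forward as the wrong quantity. The sample size section and the hypothesis both concern group differences, which is not what the named term estimates.

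**Working it through.** **Inputs.** From the article: N = 100, standardised difference 0.6, 10% loss, two-sided alpha 0.05, follow-up at weeks 4, 12, 26 and 52, and strength at weeks 0 and 12. The text says "participants will be randomised into one of two intervention groups: PHYSIOTHERAPY or SHOCKWAVE" but gives no ratio. Assumed here: 1:1 allocation, 45 evaluable per arm, SD 1, complete data, and one common correlation among all visits (0.5, with 0.3 and 0.7 as the range).

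**Step 1: the plan's own figure.**

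- Per arm: n = 2(1.960 + 0.842)² / 0.6² = 43.6, so 44. After 10% loss, 44 / 0.9 = 48.9, so 49, or 98 in total.
- Power with 45 per arm: 0.6 × √(45/2) = 2.846, and Φ(2.846 − 1.960) = 81.2%. With the noncentral t on 88 df it is 80.4%.

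The stated 80% reproduces. It is the power for a difference in means, not for a change in that difference.

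**Step 2: what the interaction estimates.** Let G = 1 for physiotherapy, and let j index the follow-up visits:

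E(Y at visit j) = α_j + βG + γ_jG + λ·baseline + κ·age stratum, with γ = 0 at the reference visit.

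The group difference at visit j is δ_j = β + γ_j. At the reference visit it is β. Hence γ_j = δ_j − δ_ref, which is a difference between two treatment effects.

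**Step 3: constant effect of 0.6 SD at all four visits.** Then γ_j = 0.6 − 0.6 = 0. With 4,000 simulated trials per row:

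| Assumed correlation | Interaction test (3 df) rejects | Adjusted week-52 difference rejects |
|---|---|---|
| 0.3 | 4.8% | 84% |
| 0.5 | 4.5% | 90% |
| 0.7 | 5.0% | 97% |

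The mean interaction coefficients were within 0.003 of zero. The week-52 contrast averaged 0.60.

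**Step 4: effect that differs at week 4.** Take week 4 as reference and a later effect of +0.6, with positive values favouring physiotherapy:

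| Week-4 effect | Coefficient at later visits | Ratio to true 0.6 |
|---|---|---|
| −0.6 | 1.20 | 2.0 |
| −0.3 | 0.90 | 1.5 |
| −0.1 | 0.70 | 1.17 |
| 0 | 0.60 | 1.0 |
| +0.3 | 0.30 | 0.5 |

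The simulated means agree to within 0.01. In the first row, taking week 52 as reference instead gives 0.6 − 0.6 = 0 at weeks 12 and 26, and −0.6 − 0.6 = −1.2 at week 4. The same data give different answers according to a choice that the article does not state.

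**Step 5: eccentric strength.** Once week 0 is a covariate, only week 12 remains as a response. With one visit there is no γ_j to estimate.

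**Step 6: the right quantity is in the same model.** In one fitted data set of 4,000 participants with a constant 0.6 effect, the group coefficient (week 4) was 0.592 and the interaction coefficients were −0.010, −0.031 and −0.005. Adding them gives 0.582, 0.561 and 0.587 at weeks 12, 26 and 52, which are the visit-specific effects.

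**The case against.** The strongest reply is that the parenthesis is shorthand: the model contains a group-by-time term, and the group difference at each visit is taken from it. The stated focus on between-group effects with confidence intervals supports this, since an omnibus interaction test gives no such interval. So do the power statement and the hypothesis. Step 6 shows that the model yields these contrasts. The strength outcome can be argued the same way: a literal interaction is impossible there, so the sentence may never have been meant literally. This is plausible as intent. But the sentence names the interaction itself as the estimator, and an analyst who follows it reports the wrong term. It is a misstated rule, not detail left to an analysis plan.

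A second reply is that the interaction equals the effect when week 0 is a response and the reference level. That is correct: in the large fitted data set it gave 0.56 to 0.59 for a true 0.6. But the text adjusts for baseline and lists only follow-up visits.

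Other replies limit the consequences. VISA-H also has a responder analysis, so a constant benefit would not go wholly unseen. The global rating of change, if analysed as ordinal, does not use this term. The outcome SD needed for a later sample size does not depend on it. The trial is a pilot. All of this stands. The correlations are assumptions, so the power figures are illustrative, although the zero under a constant effect follows from the algebra.

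A reader might go further and infer that the term doubles the effect under the plan's own hypothesis. The document does not support that. It gives no sizes and puts the early shockwave advantage only as a possibility. Doubling needs a week-4 effect equal and opposite to the later one, with week 4 as reference.

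**Conclusion.** The point holds as a misstatement of the estimator. Taken literally, the named term is zero under a constant effect, whatever the correlation. The interaction test then rejects at about the 5% alpha level, against roughly 84% to 97% for the adjusted 52-week contrast under correlations of 0.3 to 0.7, 45 per arm and complete data.

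With week 4 as reference, the coefficient differs from the later effect by exactly the week-4 effect. It is inflated if shockwave is better early, reduced if physiotherapy is, and unchanged if there is no early difference. It varies with an unstated reference visit, cannot be estimated for strength, and is not the quantity behind the 80% power figure. If visit-specific contrasts were intended, the analysis is sound and only the wording is at fault.

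**What to change.** Replace the parenthesis with a statement along these lines:

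- The model includes group, visit, group × visit, baseline value and age stratum.
- The treatment effect is the adjusted between-group difference at each follow-up visit, with 95% CI, taken as a contrast from this model (the group coefficient plus the interaction coefficient for that visit).
- The interaction test only describes whether the effect varies over time.
- For eccentric strength, the effect is the baseline- and age-adjusted group difference at week 12.

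The cost is a short wording change in the protocol or analysis plan and a different contrast in SPSS. No new data are needed and the sample size stands. The change should be recorded before the data are analysed by group.

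### Ordinal and responder outcomes are analysed without the age stratum or available baselines, and the primary global rating has no named effect with CI on its full 7-point scale

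*Protocol article*

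**What the plan says.** All of the following comes from the protocol article.

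- **Aim of the analysis (Treatment effects).** Data from weeks 4, 12, 26 and 52 are analysed "focussing on between-group treatment effects (with 95% confidence intervals").
- **Continuous outcomes (same section).** Linear mixed models, adjusted for baseline and for age as the stratification variable.
- **Ordinal outcomes (same section).** "Ordinal data will be analysed using the Mann Whitney U test at each timepoint". No covariate, stratification, effect measure or interval is named. The section accepts that repeated testing raises the type I error, but says this concerns only certain secondary outcomes.
- **Responders (same section).** A responder has a 12-point change on the VISA-H, or a global rating of much improved or better. Risk ratio, risk difference and number needed to treat are reported with 95% CIs. Significance is judged by chi-square, with no stratification mentioned.
- **Design (Randomisation and allocation).** "Randomisation will be stratified for age", split at 50 years.
- **Outcomes (Table 2).** The global rating of change, a 7-point Likert scale, is the first primary outcome and has no week-0 value. "Sitting tolerance (5-point scale") and the 6-point activity scale are secondary and are both collected at week 0.

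**The concern.** The section sets one standard for continuous outcomes and a lower one for the others. Information that the trial already holds (stratum and baseline score) enters the mixed models but not the ordinal or responder comparisons. For an ordinal outcome with a baseline, chance imbalance at week 0 then stays in the comparison and precision is lost.

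The second issue is the form of the result. The pilot is meant to supply effect estimates for a definitive trial. A Mann-Whitney test reported as written gives a p-value, so the global rating has no stated effect on the scale on which it is defined.

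Third, the remark that repeated ordinal testing touches only secondary outcomes does not fit Table 2, where the ordinal global rating is primary.

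**Working it through.** **1. The plan's own figure.** The Sample size section says "A sample size of 100 would provide 80% power to detect a between-group standardised mean difference of at least 0.6 on continuous outcome measures", "allowing for a 10% loss to follow up". The Treatment effects section adds "Alpha will be set at 0.05 using a two-tailed hypothesis". The allocation ratio is not stated, so 1:1 is assumed. The two-sample t-test needs 44.6, so 45 per arm; 90 / (1 − 0.10) = 100. Power at 45 per arm is 80.4%. The figure reproduces. It refers to continuous outcomes, and 45 analysed per arm is used below.

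**2. Unused baseline (sitting tolerance, activity scale).** The documents give no baseline correlation, so it is varied. On a continuous scale, adjustment multiplies the variance by 1 − ρ².

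| Assumed ρ | 1 − ρ² | Power at SMD 0.6, 45 per arm (80% unadjusted) |
|---|---|---|
| 0.3 | 0.91 | 84% |
| 0.5 | 0.75 | 90% |
| 0.7 | 0.51 | 98% |

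For a 5-level ordinal outcome with an assumed latent shift of 0.5 SD, simulation compared Mann-Whitney with a baseline-adjusted rank ANCOVA, which stands in for ordinal regression.

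| Assumed ρ | Mann-Whitney | Baseline-adjusted |
|---|---|---|
| 0.3 | 56% | 59% |
| 0.5 | 60% | 69% |
| 0.7 | 60% | 82% |

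Type I error was near 5% for both. Mann-Whitney does not use the baseline, so its power should not change with ρ; 56% against 60% is simulation noise. The gap within each row is what counts: about 3, 9 and 22 points. A rerun for this write-up gave the same pattern of gaps.

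None of this applies to the global rating, which has no week-0 score.

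**3. Unused age stratum.** Simulation of a 7-category outcome: 90 analysed, 5,000 runs, assumed category shares, latent shift 0.6 SD for power. Mann-Whitney is compared with the age-stratified van Elteren test.

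| Assumed age effect (SD) | Type I error, Mann-Whitney / van Elteren | Power, Mann-Whitney / van Elteren |
|---|---|---|
| 0 | 5.0% / 4.9% | 76% / 76% |
| 0.3 | 5.1% / 5.4% | 75% / 76% |
| 0.5 | 4.2% / 5.0% | 76% / 77% |
| 0.8 | 3.7% / 4.9% | 71% / 76% |

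A cost appears only at a large age effect, and there the unstratified test is conservative.

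**4. What the responder analysis gives for the global rating.** With assumed rates of 40% and 60% and 45 per arm:

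- Risk difference: 0.20 ± 1.96 × √(0.24/45 + 0.24/45) = 0.20 ± 0.202, so about −0.2 to 40 percentage points.
- Risk ratio: 1.50, with SE of its log √(0.6/(45 × 0.4) + 0.4/(45 × 0.6)) = 0.219, so 95% CI 0.98 to 2.31.

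An estimate with a CI therefore exists, but it is wide, dichotomised and unadjusted for age.

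**5. What a full-scale estimate would look like.** A proportional-odds model with age stratum (150 simulated trials, 0.6 SD shift, 0.3 SD age effect) gave a median log odds ratio of ln 2.82 with half-width 0.767. The common odds ratio is about 2.8 (95% CI about 1.3 to 6.1).

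**6. Repeated testing.** The global rating is tested at four visits. If the tests were independent, the chance of at least one false positive would be 1 − 0.95⁴ = 18.5%; correlation between visits lowers it.

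**The case against.** The strongest reply is that the primary outcome is not left without an estimate. The responder paragraph gives the global rating three effect measures with 95% CIs. A reader might infer that the pilot yields only a p-value for one of its two primary outcomes; the document does not support that. This part of the reply stands in full.

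A reader might also infer that Mann-Whitney cannot deliver an effect. It can: a Hodges-Lehmann shift or a probability of superiority may accompany it. Which measure to report could reasonably be settled in an analysis plan that is not shown. This stands in part. The missing full-scale measure is thus the lesser limb; the choice of unadjusted tests, by contrast, is fixed in the article.

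A third tempting reading is that ignoring the stratum invalidates the tests. It does not: type I error was not inflated beyond simulation noise, and power hardly moved for age effects up to 0.5 SD. Nor does the protocol call age prognostic. Its reason for stratifying is that menopause-related factors might change response to parts of treatment. That is closer to effect modification, which a main-effect covariate would not address.

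Finally, this is a declared pilot, and the section itself concedes that non-parametric tests have lower power. That is fair, but the concession does not explain leaving out week-0 values that are already collected.

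**Conclusion.** The point holds as one of efficiency and reporting, not validity. The ordinal and responder analyses omit the age stratum, and ordinal secondary outcomes with a week-0 value omit that value, while continuous outcomes get both adjustments. The material loss is precision on those secondary scales: about 9 points of power at an assumed correlation of 0.5, about 3 at 0.3 and about 22 at 0.7, all for an assumed 0.5 SD shift and 45 per arm. Omitting the age stratum costs roughly 0 to 1 point unless age is strongly prognostic (about 5 points at 0.8 SD).

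For the global rating, what is missing is a named effect with CI on the full 7-point scale; the dichotomised estimates are planned. The remark confining repeated ordinal testing to secondary outcomes is inconsistent with Table 2.

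The article does not list which outcomes count as ordinal. The conclusion treats the 5-, 6- and 7-point scales as ordinal, which is the natural reading. If the global rating was meant for the mixed model, the text should say so.

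**What to change.** 1. Analyse ordinal outcomes by proportional-odds regression with arm, age stratum and the scale's own week-0 value where one exists. For the global rating use the age stratum and, optionally, baseline VISA-H.
2. Fit the model separately at each visit, or fit one model across visits with a participant random effect or GEE/robust variance. A pooled arm-by-visit model without such a term would treat up to four ratings per participant as independent.
3. Report the common odds ratio with 95% CI at each visit. Keep Mann-Whitney as a sensitivity analysis. A van Elteren test with a rank-based effect and CI is an acceptable alternative to the age-stratum adjustment.
4. For responders, report Mantel-Haenszel risk ratio and risk difference stratified by age, with the Cochran-Mantel-Haenszel test in place of chi-square.
5. Correct the remark on type I error so that it recognises the global rating as primary.

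**Cost:** a change of analysis wording, a check of the proportional-odds assumption on scales that may be sparse at about 45 per arm, and slightly more analysis work. Sample size and data collection are unchanged.

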**Methods:**

The study is an assessor-blinded, pilot randomised controlled trial (RCT). One hundred participants with PHT will be recruited from the local community and sporting clubs. Participants will be randomised to receive six sessions of either individualised physiotherapy or ESWT, with both groups also receiving standardised education and advice.

Primary outcomes will be global rating of change on a 7-point Likert scale, and the Victorian Institute of Sport—Hamstring (VISA-H) scale, measured at 0, 4, 12, 26 and 52 weeks. Secondary outcomes will include sitting tolerance, the modified Physical Activity Level Scale, eccentric hamstring strength, modified Tampa scale for kinesiophobia, the Örebro Musculoskeletal Pain Screening Questionnaire Short Form (ÖMPSQ-SF), Numerical Pain Rating Scale (NPRS) for average and worst pain, participant adherence, the Pain Catastrophizing scale, satisfaction scores, and quality of life. Data will be analysed on an intention to treat basis, with between-group effects estimated using linear mixed models for continuous data and Mann Whitney U tests for ordinal data.

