**Primary outcome measures**	
1. Global rating of change scale (7-point Likert scale)	4, 12, 26, 52
2. VISA-H (8-item questionnaire)	0, 4, 12, 26, 52

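### The plan's reassurance about Type I error fails on both counts: repeated Mann-Whitney testing reaches a primary outcome, and lower power offsets no Type I error

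*Protocol article*

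**What the plan says.** **Outcomes.** The abstract of the protocol article names two primaries: "Primary outcomes will be global rating of change on a 7-point Likert scale, and the Victorian Institute of Sport—Hamstring (VISA-H) scale". Table 2 lists their measurement weeks as "1. Global rating of change scale (7-point Likert scale) 4, 12, 26, 52" and "2. VISA-H (8-item questionnaire) 0, 4, 12, 26, 52". The global rating therefore has four follow-up values and no baseline value.

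**Analysis.** The Treatment effects section gives two main routes. Continuous outcomes go to a linear mixed model that adjusts for baseline and age stratum, with the group-by-time interaction as the treatment effect. Ordinal outcomes go to a Mann-Whitney U test at each visit. Responder status on both primaries is also tested by chi-square. On the significance level: "Alpha will be set at 0.05 using a two-tailed hypothesis". No primary visit, order of testing or adjustment is stated.

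**Multiplicity.** The section takes up the repeated Mann-Whitney tests itself: "It is acknowledged that this will increase the Type 1 error rate however this only applies to some secondary outcomes". It continues that this "is offset in part by the lower power associated with non-parametric tests".

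**Power.** The Sample size section claims "80% power to detect a between-group standardised mean difference of at least 0.6 on continuous outcome measures such as the VISA-H", with 100 participants and 10% loss.

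**The concern.** The section admits an inflated error rate and then gives two reasons not to worry. Neither survives comparison with the rest of the article.

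The first reason is that only secondary outcomes are affected. A 7-point Likert rating is naturally read as ordinal, which sends a primary outcome to four unadjusted tests. The second reason treats low power as compensation for false positives, which it is not.

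At stake is the error rate on a primary outcome. A report that follows this text could present a significant global rating at any one of four visits as a primary result, together with an assurance that the primary outcomes are unaffected. Because the article argues the point explicitly, this is a wrong statement and not a detail left to an analysis plan.

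**Working it through.** **1. The stated power.** Inputs: 100 participants, 10% loss, standardised difference 0.6, two-sided alpha 0.05 (Sample size; Treatment effects). Equal allocation is assumed, so 45 per arm remain.
- Normal approximation: power = Φ(0.6 × √(45/2) − 1.96) = Φ(2.846 − 1.960) = Φ(0.886) = 81.2%. The t-test calculation gives 80.4%.
- In reverse: n per arm = 2 × (1.960 + 0.842)² / 0.6² = 43.6, rounded up to 44. The total is 88, and 88/0.9 = 97.8, or 98 against 100 planned.

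The 80% reproduces, so the sample size is not at issue.

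**2. Which route the global rating takes.** It is a participant's rating of change since baseline, and Table 2 gives it no week-0 value. A model that adjusts for baseline values therefore has nothing to adjust for. The remaining main route is Mann-Whitney at weeks 4, 12, 26 and 52, which is four tests on a primary outcome. If the authors meant a mixed model for it, the model as described does not fit. The section needs correction on either reading.

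**3. Whether low power offsets Type I error.** Size is the rejection rate when there is no effect. Power is the rejection rate when there is one. Lowering the second does not lower the first.
- In 20,000 simulated null trials (45 per arm, an assumed 7-category distribution, tie-corrected Mann-Whitney), each test rejected in 4.8% to 5.3% of trials. The Monte Carlo standard error is √(0.05 × 0.95/20,000) = 0.15 percentage points, so this is the nominal 5%.
- What changes is Type II error. At a relative efficiency of 0.955, power for a 0.6 difference is Φ(0.6 × √(45 × 0.955/2) − 1.96) = 79%. At 0.864 it is 75%.

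**4. Family-wise error.** For k independent tests at 0.05 it is 1 − 0.95^k:
- k = 4: 1 − 0.8145 = 18.5%
- k = 5: 1 − 0.7738 = 22.6%
- k = 8: 1 − 0.6634 = 33.7%

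Repeated measures on the same people are correlated, and the article gives no correlations. The values below are assumptions. Main entries come from the simulation in step 3, with t-tests standing in for VISA-H. Entries in brackets come from 400,000 draws of correlated normal test statistics.

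| Tests counted | Independent | r = 0.3 | r = 0.5 | r = 0.7 |
|---|---|---|---|---|
| Global rating, 4 visits | 18.5% | 17.8% | 16.0% | 14.1% (13.0%) |
| Plus one VISA-H test (5) | 22.6% | 21.8% | 19.7% | 17.5% |
| Plus VISA-H at 4 visits (8) | 33.7% | 31.8% | 28.0% (26.9%) | 23.2% (20.9%) |

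Here r is the between-visit correlation. The between-outcome correlation was set to 0.3, 0.5 and 0.6 in turn (0.7 for the bracketed entries in the last column). The chi-square responder tests are not counted and would add to these figures.

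**The case against.** **The article never calls the global rating ordinal.** This is true. A mixed model without a baseline term could be fitted to it, and the secondary-only remark may mean that the authors intended this. What is certain is that the outcome table, the two analysis routes and the multiplicity remark do not agree. That is enough for the point, but it means the fix must start by stating the analysis of this outcome.

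**Eight primary tests at 0.05.** A reader might infer these from two primaries and four visits. The text does not establish it, since a group-by-time interaction allows one overall test for VISA-H. The five-test row is therefore as legitimate as the eight-test row, and 33.7% is an upper figure that also needs independence.

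**Any pattern of results would support the hypothesis.** A reader might infer this because the Discussion expects physiotherapy to do better from 12 weeks and allows that shockwave may do better before then. It does not follow: no difference, or a shockwave advantage, from week 12 would contradict the stated hypothesis.

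**The power claim is misleading.** A reader might infer this too, but the claim is limited to continuous outcomes, and it reproduces.

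**The offset is only claimed in part.** The qualifier is there, but it does not help, because the part that is offset is zero.

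**This is a pilot.** The article says that it is not fully powered, aims to inform a later trial, and focuses on effects with 95% confidence intervals. This stands and lowers the consequence. It does not remove the point, because the same article sets a two-sided 0.05 level, plans significance tests and says it will test a superiority hypothesis.

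**Conclusion.** Both parts of the justification are wrong as written. The secondary-only statement conflicts with the abstract and Table 2. The low-power argument is an error of principle and depends on no assumption.

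The size attributable to the text is the four-test figure: 18.5% if independent, and about 13-18% under assumed between-visit correlations of 0.7 to 0.3. It rests on reading the 7-point scale as ordinal. Across both primaries the figure is about 17-23% or about 21-34%, depending on whether VISA-H is tested once or at each visit, which the article leaves open.

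The 80% power statement for VISA-H stands. Given the pilot status, this is a correction that should be made and not a flaw that invalidates the trial.

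**What to change.** 1. Delete the clause confining the inflation to secondary outcomes and the clause about lower power.
2. State how the global rating is analysed. If by Mann-Whitney at each visit, say that the inflation affects a primary outcome.
3. Then choose one of two courses:
   - Name one primary visit at 12 weeks or later, the period of the main hypothesis. Test the two primaries there in a fixed order or with Holm's procedure. Report all other visits as estimates with 95% confidence intervals and no claim of significance.
   - Or state that all tests in this pilot are exploratory, and word the Discussion's hypothesis to match.
4. State whether VISA-H is tested by one interaction test or by visit.

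**Cost.** Wording only, with no extra participants. A fixed order leaves the first-ranked outcome at 0.05. Holm tests the smaller p-value at 0.025, where 45 per arm give about 71% power for a 0.6 difference.

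The choice would come late: recruitment began in July 2021, this version is dated 7 March 2023, and the primary researcher receives allocations. It should therefore be recorded as a dated change, made before any analysis with group labels and disclosed in the report.
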